### Outcomes and Measures

Clinical outcomes will be assessed using validated screening scales for self-reported symptoms, including Perceived Stress Scale (PSS-10; a score of ≥10 indicates a likely moderate or high stress) [55], the 7-item GAD scale (GAD-7; a score of ≥10 indicates likely generalized anxiety disorder) [56], the Patient Health Questionnaire-9 (PHQ-9; a score ≥10 indicates likely MDD) [57], and the Brief Resilience Scale (BRS; mean scores ranging from 1.00 to 2.99 indicate low resilience, from 3.00 to 4.30 suggest normal resilience, and from 4.31 to 5.00 suggest high resilience) [58,59].Validated scales have been chosen to better understand self-reported symptoms and potential symptom severity and to screen for the likely presence of psychopathology. These scales are not intended as diagnostic tools but instead are to identify risk factors and early symptoms of potential mental disorders such as depression and anxiety disorders. In addition, we will assess burnout using the Maslach Burnout Inventory (MBI) [60]. The MBI-Educators Survey will be used in this case, which is a version of the original MBI for use with educators, including teachers, administrators, other staff members, and volunteers working in any educational setting [61]. The primary outcome measures will be prevalence of moderate-to-high stress, burnout, likely GAD, likely MDD, and low resilience at baseline in subscribers of Wellness4Teachers. Other primary outcome measures will be changes in prevalence of moderate-to-high stress, burnout, likely GAD, likely MDD, and low resilience as well as changes in mean scores on the PSS-10, MBI, GAD-7, PHQ-9, and the BRS from baseline to 6 weeks, 3 months, and 6 months. Secondary outcome measures will include sociodemographic, clinical, and professional correlates of moderate-to-high stress, burnout, likely MDD, likely GAD, and low resilience among subscribers of Wellness4Teachers at baseline. An exploratory outcome will be a measurement of the adoption of the Wellness4Teachers program by teachers in Alberta and Nova Scotia. This will be assessed by measuring the proportion of the target population (teachers in Alberta and Nova Scotia) who subscribe to the daily supportive text messages.

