### Sample Size Estimation

With a teacher population of approximately 45,000 in Alberta and Nova Scotia, using a web-based script [62], we estimate that the sample size needed for our prevalence estimates with a 95% CI and 3% margin of error for moderate-to-high stress, burnout, likely GAD, likely MDD, and low resilience among teachers in Alberta and Nova Scotia is 1043. Based on the response rates achieved for the Text4Hope and Text4Mood programs in Alberta [35,63,64], we expect a maximum of 20% survey completion rate for the Wellness4Teachers program. Thus, to achieve the 1043 completed surveys at baseline, we expect to enroll 5515 teachers on the Wellness4Teachers program within 12 months.

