### Statistical Analysis

Quantitative data from the surveys will be analyzed using SPSS (version 25, IBM Corp) [65]. Descriptive statistics will be provided for demographic, clinical, and burnout-related variables based on the province of residence. Cross-tabular analyses using the chi-square test will explore the differences between elementary and high school teachers with respect to demographic, clinical, and professional variables. Descriptive characteristics will be presented as numbers and percentages, and a 2-tailed *P*≤.05 will be used to determine statistical significance for all analyses. We will use the chi-square test and logistic regression analysis to identify demographic, clinical, and work-related correlates of anxiety, depression, stress, low resilience, and burnout for elementary and high school teachers separately. Furthermore, we will assess the impact of the Wellness4Teachers program in reducing moderate-to-high stress, burnout, likely GAD, likely MDD, and improving resilience among Wellness4Teachers subscribers by assessing the mean changes in these parameters from baseline to 6 weeks, 3 months, and 6 months using the 2-tailed paired *t* test. To assess the effects of the intervention against a control group, we will choose a defined period of 3 months during the study period (eg, from the beginning of November 2022 to the end of January 2023) and compare the prevalence and mean scores on standardized scales for stress, burnout, anxiety, and depression at 6 weeks for subscribers who have received the daily supportive text messages for 6 weeks (intervention group) to the baseline prevalence and mean scores on the same scales for new subscribers during the period (control group). Surveys with more than 50% missing responses will be omitted from data analysis. For the included survey responses, there will be no imputation for missing data, and the analysis and results will be based on completed survey data.

We will analyze qualitative data (obtained by audio recording and transcribing responses from key informant interviews) using thematic analysis with NVivo (version 9; QSR International). The results will be reported as themes and subthemes supported by verbatim quotes.

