### Hypothesis

We hypothesize that the prevalence of stress, burnout, symptoms of anxiety and depression, as well as low resilience among teachers in Alberta and Nova Scotia would be comparable to those reported in other jurisdictions [8,66].

We also hypothesize that factors such as gender, sex, age, marital status, number of years teaching, grade of teaching, and school type (elementary vs high school) will have an association with burnout and other psychological disorders in teachers [67-72].

Finally, we hypothesize that the Wellness4Teachers program will reduce the prevalence and severity of stress, anxiety, depression, burnout, and low resilience symptoms among teachers by at least 20% [43]. This specific hypothesis is based on related research findings. In the 2 RCTs conducted in Ireland and Canada, there was a greater than 20% reduction in depression symptom scores in the intervention group compared to the control group [73,74]. Furthermore, for the Text4Hope program in Alberta, there was a greater than 20% reduction in anxiety symptom scores in subscribers at 6 weeks and 3 months [36,37].

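### Correlates are tested only on yes/no categories although full baseline scores are collected; score-based models added alongside would recover power for the second hypothesis

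*Protocol article*

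**What the plan says.** The Statistical Analysis section states: "We will use the chi-square test and logistic regression analysis to identify demographic, clinical, and work-related correlates of anxiety, depression, stress, low resilience, and burnout". These analyses are run separately for elementary and high school teachers, with a two-sided 5% criterion throughout. No model of the scores themselves is named for this purpose.

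Outcomes and Measures defines the target the same way: "Secondary outcome measures will include sociodemographic, clinical, and professional correlates of moderate-to-high stress, burnout, likely MDD, likely GAD, and low resilience". It gives the cuts for four scales: PSS-10 ("a score of ≥10 indicates a likely moderate or high stress"), GAD-7 ("a score of ≥10 indicates likely generalized anxiety disorder"), PHQ-9 ("a score ≥10 indicates likely MDD") and BRS ("mean scores ranging from 1.00 to 2.99 indicate low resilience"). Burnout is measured with the educators' version of the MBI.

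The second hypothesis is that gender, age, marital status, years of teaching and similar factors "will have an association with burnout and other psychological disorders in teachers". No effect size is attached to it. The sample size of 1043 is set for prevalence precision alone: "95% CI and 3% margin of error for moderate-to-high stress, burnout, likely GAD, likely MDD, and low resilience".

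For the programme's effect, by contrast, the article uses the scores. It lists changes in mean scores as primary outcomes, applies paired t tests, and compares both prevalence and mean scores at 6 weeks.

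**The concern.** Cutting a numeric score at a threshold treats everyone on the same side of it as identical, which discards information about association. The further the cut lies from the middle of the distribution, the more is lost. The correlates belong to the first main objective, are a secondary outcome and carry the second hypothesis. They are examined within each school type, in a sample that was not sized for them.

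A real association with, say, gender or years of teaching could therefore be missed, or could appear for one outcome and not another only because the cuts fall at different points. Stress is most exposed if most subscribers are above its threshold. The scores are already in the dataset, so the loss is avoidable.

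**Working it through.** **The plan's own figure.** n0 = 1.96² × 0.25 / 0.03² = 1067.1. With the finite population correction for 45,000 teachers, 1067.1 / (1 + 1066.1/45,000) = 1042.4, which rounds up to 1043. The figure reproduces, and it concerns prevalence only.

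**Inputs from the article.** Two-sided alpha is 0.05, with 1043 baseline surveys. Illustrative prevalences are 88.0% (stress), 52.1% (depression) and 46.5% (anxiety), all from new Text4Hope subscribers (Wellness4Teachers Program section), and 33.3% (high burnout in a cited teacher study, Background). No prevalence for low resilience was available for this check.

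**Assumptions.** Scores are normal. School types are split evenly, so 1043/2 is about 521 each. The factor has two levels, and the true difference d is in SD units. The article gives none of these.

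**Information kept by the cut**, φ(z)² / [p(1−p)], where z is the normal quantile at prevalence p:

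- 52.1%: 0.3984² / 0.2496 = 0.636
- 46.5%: 0.3974² / 0.2488 = 0.635
- 33.3%: 0.3635² / 0.2221 = 0.595
- 88.0%: 0.2000² / 0.1056 = 0.379

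**Power at n = 521, d = 0.25, even factor split.** Full score: 0.25 × √(521 × 0.25) = 2.853, and Φ(2.853 − 1.96) = 81%. For the cut score, multiply 2.853 by the square root of the information kept:

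- Depression and anxiety: 2.853 × 0.797 = 2.27, power 62%
- Burnout: 2.853 × 0.771 = 2.20, power 60% (59% by the direct two-proportion formula)
- Stress: 2.853 × 0.616 = 1.76, power 42% (41% by the direct formula)

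A simulation of logistic against linear regression (1500 runs, same setting) gave 0.65 against 0.82 for depression, 0.60 against 0.81 for burnout and 0.42 against 0.83 for stress.

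**How the loss varies** (percentage points, even factor split):

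| Setting | Full-score power | Loss, prevalence 33.3 to 52.1% | Loss, prevalence 88.0% |
|---|---|---|---|
| n = 521, d = 0.10 | 21% | 6 to 7 | 10 |
| n = 521, d = 0.17 | 49% | 15 to 17 | 27 |
| n = 521, d = 0.25 | 81% | 19 to 22 | 40 |
| n = 521, d = 0.28 | 89% | 17 to 20 | 40 |
| n = 521, d = 0.40 | 99.5% | 4 to 6 | 21 |
| n = 1043, d = 0.30 | 99.8% | 3 to 4 | 16 |
| n = 1043, d = 0.40 | 100% | about 0.1 | 3 |

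With a 25/75 factor split at n = 521 and d = 0.25, full-score power is 70%. It falls to about 50% for depression and anxiety and to 45 to 50% for burnout. For stress it falls to 27 to 38%. The ranges depend on whether the smaller or the larger group scores higher.

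**Skewed scores.** In a simulation with gamma-distributed scores (n = 522, about 80% full-score power), cut-score power was 53 to 59% at prevalences of 20 to 50%, and 19% at 88%. The loss is not an artefact of assuming normality.

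**The case against.** The strongest reply is that the planned analysis answers the declared question. The first main objective (Study Aims, Textbox 1) and the secondary outcome both ask for correlates of the categories, and logistic regression on case status estimates exactly that. A regression of the mean score asks which factors shift the average, which is a related but different question. This stands. A reader might infer that the plan contradicts itself, or that the logistic models should be reduced to a descriptive role; the documents support neither.

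A reader might also argue that the article's remark about the scales not being diagnostic undermines the cuts. It does not: the same sentence gives identifying risk factors as a purpose of the scales.

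Second, it is tempting to quote a loss of 15 to 40 points outright. The article gives no effect size, factor split or power target for this hypothesis, and the table shows losses from near zero upward. The 40-point end rests on 88.0% stress in a general-population programme during the pandemic, which may not carry over to teachers. School type itself is compared across all teachers, so the pooled sample applies to that factor. These points limit the size of the claim without removing it.

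Third, supplementary score models might sit in a fuller analysis plan. That is possible, but the article does name its method for the correlates, and a score-based model is not part of it.

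**Conclusion.** The point holds as an avoidable inefficiency in a secondary analysis. The information kept is about 64% at prevalences of 46.5 to 52.1%, 60% at 33.3%, and 38% if stress prevalence is near 88.0%. Where the full-score test would have about 50 to 90% power, the loss is about 15 to 22 points for mid-scale cuts and up to about 40 for stress. With an even factor split, that means differences of roughly 0.17 to 0.28 SD at about 521 per school type. Outside that range the loss shrinks, except that for stress it remains material at somewhat larger effects.

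These sizes rest on assumed normal scores, effect sizes and splits, and on prevalences borrowed from other populations. They show what may be lost and do not predict this study's power.

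**What to change.** Keep the planned chi-square tests and logistic regressions for the declared categories. In Statistical Analysis, add pre-specified multivariable linear regressions with robust standard errors, or ordinal regression if scores are skewed. The outcomes are the full baseline PSS-10, GAD-7, PHQ-9, BRS and MBI dimension scores, on the same demographic, clinical and work-related factors. State that these serve as the more powerful test of association for the second hypothesis. In Outcomes and Measures, list correlates of the scores beside correlates of the categories.

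No extra participants or survey items are needed. The cost is in reporting: burnout has three dimensions, so there are 4 + 3 = 7 score models per school type, or 14 over both. That brings more coefficients, expressed in scale points and not as odds ratios, and more tests at the 5% level. Fixing the models before the data are seen avoids a later choice between cut and full-score results.

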## Methods

### Study Design

This study will use a mixed-methods quantitative and qualitative cross-sectional survey design. Quantitative data will be collected using web-based–administered questionnaires through the University of Alberta REDCap platform [46], a secure web application for building and managing web-based surveys and databases. Qualitative data will be collected through key informant interviews.

The web-based questionnaires will be designed to collect demographic, professional, and clinical variables including stress, burnout, anxiety, depression, and resilience. Follow-up surveys will also include subscriber experience and satisfaction questions. Teachers in Alberta and Nova Scotia will be invited to subscribe to the Wellness4Teachers program through an advertisement organized in collaboration with Alberta Teachers Association, the Alberta School Boards Association, the Nova Scotia School Boards Association, and the Nova Scotia Teachers Union. The web-based surveys will be distributed to subscribers upon enrollment, at 6 weeks, 3 months, and 6 months. Key informant interview questionnaire will be developed to assess and explore the factors that contribute to stress, burnout, anxiety, and depression among teachers, the impact of the Wellness4Teachers program on the levels of these mental health variables in subscribers, and subscriber satisfaction with the daily supportive text messaging program.

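### School type is a hypothesised correlate, but the regressions are fitted separately by school type, so only an unadjusted chi-square can address it

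*Protocol article*

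**What the plan says.** The Hypothesis section of the protocol article gives a list of factors, including gender, age, marital status and years of teaching, and ends it with "grade of teaching, and school type (elementary vs high school) will have an association with burnout and other psychological disorders in teachers". The Results paragraph of the Abstract repeats school type as an expected correlate. Under Outcomes and Measures, correlates are a secondary outcome, assessed at baseline: "Secondary outcome measures will include sociodemographic, clinical, and professional correlates of moderate-to-high stress, burnout, likely MDD, likely GAD, and low resilience".

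Two sentences of the Statistical Analysis section bear on this hypothesis.

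- The comparison between the groups: "Cross-tabular analyses using the chi-square test will explore the differences between elementary and high school teachers with respect to demographic, clinical, and professional variables". Study Design describes the survey's "clinical variables including stress, burnout, anxiety, depression, and resilience", so burnout and the other conditions fall within this cross-tabulation.
- The correlates analysis: "We will use the chi-square test and logistic regression analysis to identify demographic, clinical, and work-related correlates", which the same sentence completes as "correlates of anxiety, depression, stress, low resilience, and burnout for elementary and high school teachers separately".

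The article describes no pooled regression, no school-type term and no school-type interaction.

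**The concern.** Regression is the plan's tool for looking at several correlates together. Because it is run within each school type, the one listed factor it cannot address is school type itself. What remains is a crude comparison of elementary with high school teachers. The other factors in the same hypothesis, such as gender, age and years of teaching, may be distributed differently in the two groups and may themselves be related to burnout.

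At stake is how a stated hypothesis will be read. A crude difference could reflect who teaches at each level, and a crude null could hide a difference. As written, the plan produces nothing that tells these apart. This is a choice the article makes explicitly and that fits poorly with its own hypothesis, so it is not a detail left to a fuller plan.

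**Working it through.** **1. The plan's own sample size.** The Sample Size Estimation section gives 1043 completed baseline surveys for a 95% CI, a 3% margin of error and about 45,000 teachers. It states no expected proportion; I assume 0.5.

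- n0 = 1.96² × 0.25 / 0.03² = 1067.1
- with finite population correction: 1067.1 / (1 + 1066.1/45,000) = 1042.4, rounded up to 1043

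The figure reproduces, and 1043 is used below as the number of teachers analysed.

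**2. Can school type be estimated?** Take a design matrix with four columns: intercept, two covariates and school type.

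- Elementary teachers only: rank 3 of 4
- High school teachers only: rank 3 of 4
- Both groups pooled: rank 4 of 4

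Within a group the school-type column is a multiple of the intercept. No sample size changes that, and setting the coefficients of the two separate models side by side does not give a school-type odds ratio.

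**3. How far could the crude comparison mislead?** The documents give no gender mix by school type and no burnout rate by gender, so these are assumptions: 85% women in elementary; 55% or 65% in high school; burnout 40% in women and 25% or 30% in men; no school-type effect.

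Crude burnout = share of women × rate in women + share of men × rate in men.

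| Rate in men | Women in high school | Elementary | High school | Difference (points) | Crude OR |
|---|---|---|---|---|---|
| 25% | 55% | 0.3775 | 0.3325 | 4.5 | 1.22 |
| 25% | 65% | 0.3775 | 0.3475 | 3.0 | 1.14 |
| 30% | 55% | 0.3850 | 0.3550 | 3.0 | 1.14 |
| 30% | 65% | 0.3850 | 0.3650 | 2.0 | 1.09 |

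First row in full: (0.3775/0.6225) / (0.3325/0.6675) = 0.606/0.498 = 1.22.

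**4. Check by simulation.** A binary covariate was present in 85% of elementary and 55% of high school teachers, with a log-odds effect of 0.5 to 0.7 on the outcome and a true school-type OR of 1.0 (200,000 simulated teachers). For high school against elementary, the crude OR was 0.86 to 0.81 and the adjusted OR 0.99. Reversed to elementary against high school, the crude values are 1/0.86 = 1.16 to 1/0.81 = 1.23, in line with the table. Adjustment in a pooled model removes the spurious association.

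**5. How often would that reach P≤.05?** With 1043 teachers split evenly, differences of 2.0 to 4.5 points would be significant in about 10% to 33% of studies; with a 70:30 split, in about 9% to 29%. The nominal rate is 5%.

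**The case against.** The strongest reply is that the hypothesis speaks only of an association, not an adjusted or independent one, and the planned chi-square tests exactly that. This stands. A reader might infer that the school-type hypothesis goes untested; the documents do not support that, because the cross-tabulation covers the clinical variables and burnout is one of them. Nor is that test weak against large differences: assuming 33.3% burnout in one group (a figure cited in Background) and splits from 50:50 to 70:30, its power at 1043 is 86.5% to 91.5% for a 10-point difference.

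It is also fair that the size of confounding rests on assumed inputs. They show what could happen, not that it will, and in most studies gender alone would not produce a false positive.

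Two further readings are tempting.

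- That splitting the sample wastes precision, with standard errors about √2 = 1.4 times larger. This holds only with an even split and only if each correlate has the same effect in both groups. If stratum-specific effects are wanted, a fully interacted pooled model gives the same estimates and standard errors.
- That the plan will treat a correlate significant in one group and not in the other as a difference between groups. The article proposes no such comparison and hypothesises no effect modification.

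Lastly, covariate lists and supplementary models are often left to a full plan, and nothing rules out a further pooled model. But the article does fix the split by school type, and that split is what removes the school-type coefficient.

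**Conclusion.** The point holds in a limited form. No regression the article describes can estimate the association between school type and any of the five conditions, although that association is a stated hypothesis. The hypothesis receives an unadjusted test only.

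The structural part needs no assumption: school type is constant in each planned model. The size does. On the assumed gender mix and burnout rates, the crude odds ratio would be about 1.09 to 1.22 with no school-type effect, a modest bias; other factors could add to it or offset it. The point concerns a secondary outcome. The primary outcomes and the sample size of 1043 are unaffected. It is worth acting on because the remedy costs almost nothing.

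**What to change.** Add to Statistical Analysis one pooled logistic model per condition, covering elementary and high school teachers together, with school type as a covariate alongside the other hypothesised factors (gender, age, marital status, years of teaching). Report the adjusted odds ratio for school type with its 95% CI, next to the crude comparison. Grade of teaching needs care: if entered as categories that determine school type, it brings the collinearity back, so leave it out of this model or examine it in another.

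Keep the separate models as stratum-specific output. If any claim is to be made that a correlate differs between school types, base it on a school-type interaction term in the pooled model.

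The cost is a sentence or two of text and a little extra analysis. The launch is still ahead in the article, and the variables are already planned for collection; no added participants or questions are needed.

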**Methods:**

This is a cross-sessional mixed methods study with data to be collected from subscribers of Wellness4Teachers using a web-based survey at baseline (onset of text messaging), 6 weeks, the program’s midpoint (3 months), and end point (6 months). Teachers can subscribe to the Wellness4Teachers program by texting the keyword “TeachWell” to the program phone number. Outcome measures will be assessed using standardized rating scales and key informant interviews. Data will be analyzed with descriptive and inferential statistics using SPSS and thematic analysis using NVivo.

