The relationship between burnout and health exhibits complicated pattern in the sense that poor health contributes to burnout, and burnout contributes to poor health [17]. Burnout is a risk factor for poor physical and mental well-being, and it may adversely affect health [11,18]. There is increasing evidence that burnout as a stress response represents a risk factor not only for depression but also for cardiovascular and other somatic diseases [19]. Burnout is occupational-specific dysphoria, which is different from depression—a general mental illness [5]. Burnout is regarded as a stress-related state, and the rates of clinical depression increase with the severity of burnout [19]. Burnout is also job related and dependent on the situation or condition, while depression is more general and context‐free [6]. Cross-sectional studies showed that there is a relationship between burnout and depression with greater risk of major depressive disorder (MDD) when burnout is severe [12]. Teachers with MDD also had higher levels of perceived stress, anxiety, disorder, and lower quality of life [20]; moreover, poor workplace environment was a factor associated with both increased anxiety and depressive symptoms [21]. The published results of a study reported a high prevalence of depression (49.1%) among teachers [22] as well as a relatively high prevalence of anxiety 68.0% [23].

In a longitudinal study, individual teachers who experienced an increase in the states of burnout had an increase in depression in comparison to those with decrease in burnout, which corresponded to less depression [7,24]. This was also observed in a study where 86% of the teachers who identified as burned-out met the criteria for a provisional diagnosis of depression [25].

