## Results

The Wellness4Teachers program is expected to be launched in September 2022 when the new academic year is scheduled to begin. Enrollment will last for approximately 1 year, and data collection will continue for another 6 months. Study results will be disseminated with stakeholders in the education sector in Alberta and Nova Scotia and globally through workshops, conference presentations, and peer-reviewed publications.

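### The 3- and 6-month changes, and all resilience changes, are credited to the program by an uncontrolled paired test that also picks up any school-calendar shift

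*Protocol article*

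**What the plan says.** Survey timing hangs on sign-up alone. The Abstract places the surveys at "baseline (onset of text messaging), 6 weeks, the program’s midpoint (3 months), and end point (6 months"), and Study Design repeats this: "The web-based surveys will be distributed to subscribers upon enrollment, at 6 weeks, 3 months, and 6 months". Neither section ties a survey to term or calendar date.

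The Results section says the program is "expected to be launched in September 2022 when the new academic year is scheduled to begin", and then: "Enrollment will last for approximately 1 year, and data collection will continue for another 6 months".

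Outcomes and Measures makes the changes primary: "Other primary outcome measures will be changes in prevalence of moderate-to-high stress, burnout, likely GAD, likely MDD, and low resilience", together with changes in mean scores on the five scales, at all three follow-up visits.

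Statistical Analysis assesses impact "by assessing the mean changes in these parameters from baseline to 6 weeks, 3 months, and 6 months using the 2-tailed paired" t test. It adds one comparison with a control group. Within one chosen 3-month window (November 2022 to January 2023 is the example), subscribers at 6 weeks are compared with new subscribers at baseline on stress, burnout, anxiety and depression. Resilience is not listed, and there is no counterpart at 3 or 6 months. The Limitations section does not mention the school calendar.

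**The concern.** A paired change credits the program with everything that differs between the two survey dates. For teachers, one thing that differs is the point in the school year. The protocol's own Background gives reason to expect this to matter for burnout: "Burnout is also job related and dependent on the situation or condition, while depression is more general and context"-free. The Background also names student discipline and curriculum delivery as sources of teachers' stress.

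A teacher who joins in mid-April answers the 3-month survey in mid-July. One who joins in early January answers the 6-month survey in July. One who joins at launch moves from school start to mid-autumn, December and March. If scores fall because school is out, the plan reads this as benefit. If they rise as term goes on, a real benefit may be masked. The Discussion intends the findings as evidence of effectiveness for policy makers, so the attribution matters.

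**Working it through.** **Inputs from the protocol.** Launch in September 2022; enrolment about 12 months; surveys at 6 weeks, 3 months and 6 months after sign-up; two-sided P≤.05; target of 1043 completed baseline surveys.

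**Assumptions, not in the protocol.** First sign-up on 1 September 2022; break from 1 July to 31 August (62 days); visits at 42, 91 and 182 days; a break effect of 0.3 or 0.5 SD of the change score; 200 or 400 completed pairs.

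**The plan's own figure.** 1.96² × 0.25 / 0.03² = 1067.1. With the finite population correction, 1067.1 / (1 + 1066.1/45,000) = 1042.4, rounded up to 1043. It reproduces. It is a target for baseline prevalence, so 1043 pairs would need every targeted baseline responder to answer again. The 200 and 400 pairs used here are 19% and 38% of it.

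**Step 1: who is surveyed in the break.** Counting back from July-August 2023, the sign-ups concerned are about 20 May to 20 July (6 weeks), 1 April to 1 June (3 months) and 31 December to 2 March (6 months). Sign-ups in September 2022 are surveyed on 13 October-11 November, 1-30 December and 2-31 March.

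**Step 2: net share of pairs moving from term into the break** (term-to-break minus break-to-term).

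| Sign-up pattern | 3 months | 6 months |
|---|---|---|
| Even over 365 days | 62/365 − 62/365 = 0% | 62/365 − 62/365 = 0% |
| Front-loaded, rate halving every 30-120 days | 0.5-4.1% | 4.6-12% |
| Even September-June (303 days) | 62/303 = 20.5% | 62/303 = 20.5% |

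At 6 weeks the even September-June pattern gives 42/303 = 13.9%, but there the same-period comparison offers a partial check.

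**Step 3: false significance toward benefit when the program does nothing.** With net share f, break effect d in SD of the change, and n pairs, the mean shift is f × d, so z = f × d × √n and the probability is Φ(z − 1.96). The nominal value is 2.5%.

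| f | d = 0.3, n = 200 | d = 0.3, n = 400 | d = 0.5, n = 200 | d = 0.5, n = 400 |
|---|---|---|---|---|
| 0% | 2.5% | 2.5% | 2.5% | 2.5% |
| 4.1% | 4% | 4% | 5% | 6% |
| 12% | 7% | 11% | 13% | 22% |
| 20% | 13% | 22% | 29% | 52% |

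Example: 0.20 × 0.5 × √400 = 2.0, and Φ(2.0 − 1.96) = 52%.

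**Step 4: what front-loading does.** It shrinks the summer share but gives most pairs the same move from school start to later in term. That shift is not in the table. Neither its size nor its direction can be derived from the protocol.

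**The case against.** The best defence has four parts.

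- **Missing detail.** Only an article is shown, and covariates and sensitivity analyses usually belong to an analysis plan. This is fair for the details of an adjusted model. It does not cover the method that is stated: impact on primary outcomes is read from a paired change, which credits calendar shifts to the program when carried out as written.
- **Existing control.** The same-period comparison shows that the authors saw the need for a contemporaneous reference. This stands at 6 weeks for stress, burnout, anxiety and depression, at least in the chosen window. It does not reach 3 months, 6 months or resilience.
- **Size.** Enrolment is planned over about a year, and opposite moves can offset each other. For the break effect at 3 months it is enough that as many teachers join between 1 April and 1 June as in July-August; sign-up need not be flat all year. This stands, and it is why the range starts at zero. The 20% share supposes no sign-up at all in July-August, and a September launch may equally well front-load enrolment and give the lower figures.
- **Evidence.** The Background sentence on situational dependence concerns burnout and contrasts it with depression, so it does not show that depression scores follow the calendar. This stands too, although the same section links poor workplace environment with anxiety and depressive symptoms.

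A reader might infer that the primary changes will mostly be a summer artefact favouring the program. The protocol does not support this. It gives no break dates, seasonal effect or sign-up curve, and a shift within term could work against the program.

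**Conclusion.** The point holds for the 3- and 6-month primary changes and for resilience at every visit. There the planned test cannot tell a program effect from a school-calendar shift, and nothing else in the protocol supplies a reference. For the other four constructs at 6 weeks it is partly handled.

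Under the assumed July-August break, no program effect, a 0.5 SD break effect and 400 pairs, the chance of a false finding of benefit runs from near 2.5% to about 52%. With front-loaded sign-up it reaches at most about 6% at 3 months and 22% at 6 months from the summer break alone. These are illustrations over a range, not predictions. If sign-ups cluster at launch, the calendar shift is common to most participants, its direction is unknown, and no analysis of these data alone can remove it.

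This should be changed: it affects how primary results are interpreted, and analysis wording plus a stated limitation deals with most of it.

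**What to change.** - In Statistical Analysis, replace the stand-alone paired test for program impact with a longitudinal model of the scores. Include calendar period of survey completion (part of term, or break) alongside time since sign-up, with new subscribers' baselines from the same period as the calendar reference. Apply it at 3 and 6 months and to resilience.
- State the assumption behind it: teachers who subscribe early and late are otherwise comparable. The existing 6-week comparison already relies on this.
- Pre-specify a sensitivity analysis excluding pairs in which either survey was completed in the school break. It addresses the break only, not shifts within term.
- In Limitations, state that calendar and program effects cannot be separated if sign-ups cluster at launch, and report the distribution of sign-up dates so that readers can judge.

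The cost is analysis wording and no extra participants or surveys, provided that survey completion dates are kept. The change estimates lose some precision, and the adjusted change may be smaller than the raw one.
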